### Statistics

The crossover design makes it possible to compare the two treatment modalities within the same person, thereby minimising between-patient variation. This design is appropriate because type 1 diabetes is a chronic, stable disease with slow progression. Therefore, the status of the patient in the first treatment period is assumed to be the same in the second period. To avoid a possible period effect and unwelcome fluctuations in blood glucose in relation to shift from one treatment modality to the next, registration of the primary endpoint is performed after three months in each arm. The long participation of two years per patient ensures a sufficient time of observation to minimise the risk of dealing with patients at particularly good or bad periods of their illness. Therefore, the analysis will be based on data from patients who complete the first treatment period and at least 6 months of the second treatment period. An analysis in a negative binomial distribution or Poisson model will be used to describe the number of events through a log link function as a linear function of treatment, treatment period, HbA_1c_ levels and other relevant variables (state of hypoglycaemia awareness, C-peptide status, age, duration of diabetes, daily insulin dose). Individual differences in the observation period will be adjusted for in the analysis.

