## Methods/design

### Design

The study is a Danish two-year, investigator-initiated, prospective, randomised, open, blinded endpoint (PROBE), multicentre, cross-over trial investigating the effect of insulin analogues versus human insulin on the frequency of severe hypoglycaemia (Figure 1). Patients are randomised to treatment with basal-bolus therapy with insulin detemir and insulin aspart (Levemir®/Novorapid®) or human NPH insulin and human regular insulin (Insulatard®/Actrapid®), in random order. Doses of insulin are adjusted according to individual patient need at the discretion of the investigator. Thus, a treat-to-target design is deliberately not used in order not to intervene with present glycaemic control and everyday clinical practice, which otherwise in itself will interfere with the risk of hypoglycaemia. The best obtainable glycaemic control for the individual patient is strived for in both treatment periods. The protocol did not specify the timing and number of insulin injections per day. In general, a four times daily basal-bolus regimen was selected, e.g. basal insulin before bedtime and prandial insulin before meals. Patients were instructed in insulin injection technique at the beginning of each treatment arm. Endpoints are assessed during the last 9 months of each treatment arm, the first 3 months being used for run-in on a new treatment regimen. Optional admissions for overnight plasma glucose measurements followed by three days of blinded continuous glucose monitoring (CGM) are performed after 6 and 12 months of treatment in each treatment arm.

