### Subjects

From November 2006 to June 2007 questionnaires were sent to 6112 patients with type 1 diabetes attending the outpatient clinics at Steno Diabetes Center, Hillerød Hospital, Hvidovre Hospital, Bispebjerg Hospital, Odense University Hospital, Copenhagen University Hospital (Rigshospitalet), and Aarhus University Hospital. From some centres reminders were sent once. A total of 3861 patients filled in the questionnaire (63.2%). Patients were, among other things, asked how many episodes of severe hypoglycaemia they had experienced during the last year. Patients with two or more episodes were identified (n = 720) and invited by letter to participate in the HypoAna Trial. Subjects were included in the HypoAna Trial from May 2007 to November 2009. The inclusion criteria are type 1 diabetes for more than five years, two or more episodes of severe hypoglycaemia in the previous year (defined as need for third party assistance to restore blood glucose level), age > 18 years, and a negative pregnancy test. There were no inclusion criteria regarding the pre-randomisation insulin treatment. Exclusion criteria are treated adrenal or growth hormone insufficiency or untreated hypothyroidism, myocardial infarction or coronary revascularisation, transient ischemic attack or stroke within the last three months, history of malignancy unless a disease-free period exceeding five years, history of alcohol or drug abuse, pregnancy or lactation, and women of childbearing potential who are not using chemical or mechanical contraception. Criteria for discontinuation are voluntary withdrawal of consent, pregnancy, or non-compliance with the study protocol as judged by the investigator. Discontinuing patients are not substituted, but data on discontinuing patients are included in data analyses on an intention-to-treat basis. The study was approved by The Regional Committee on Biomedical Research Ethics (# H-KA-20070008) and the Danish Medicines Agency (# 2612–3397). The study is registered at http://www.clinicaltrials.gov (# NCT00346996). The Study will be conducted in accordance with the Helsinki Declaration.

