### Power calculation

In the power calculation, the number of events in each treatment period is assumed to be distributed according to a Poisson model. No period effect exceeding the 3 months of run-in is assumed. Based on the total number of observed events for each individual patient, the number of events for a treatment period is reduced to a binomial distribution:

Binomial (total number of events, λ_human insulin_/(λ_human insulin_ + λ_insulin analogue_)), which under the null hypothesis of no difference in event rate between insulin analogues and human insulin becomes binomial (total number of events, ½). The power calculations are thus performed with the use of an exact test of number of events in a binomial distribution with the probability of p = 1/2 versus alternatively with the probability of P = λ_human insulin_/(λ_human insulin_ + λ_insulin analogue_) = 1/(1+ λ_insulin analogue_/λ_human insulin_). The sample size calculation thus indicates the total number of events needed. The study population is selected to be patients with an expected increased risk of severe hypoglycaemia. Assuming an incidence of 2.8 severe hypoglycaemic events per patient-year, corresponding to 2.09 per 9 months treatment period, and setting minimal relevant difference (MIREDIF) to a reduction in the incidence of severe hypoglycaemia of 15% (based on the conclusion of the American Diabetes Association Workgroup on Hypoglycemia ”that any significant reduction in severe hypoglycemia (that requiring the assistance of another individual), even by as little as 10–20%, would be advantageous” [26]), this will correspond to a reduction in the relation between human and analogue insulin of: λinsulin analogue/λhuman insulin = 0.85. Setting power to 80% and a test level of 5%, the total number of events needs to be 1220. With an expected number of events of 2.09 + 1.75 (1.75 = 2.09 x 15% reduction in incidence of severe hypoglycaemia) = 3.84 events per 18 months’ treatment, this corresponds to a need for 315 patients. With an expected dropout rate of 15%, 370 patients need to be included.

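### The primary analysis population is defined in two incompatible ways: discontinuing patients are included by intention to treat, yet anyone leaving before about month 18 is excluded

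*Protocol article*

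**What the plan says.** Two sections of the protocol article state who is analysed.

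- **Subjects**: patients who discontinue are not replaced, but "data on discontinuing patients are included in data analyses on an intention-to-treat basis". The same section gives the reasons for leaving: "Criteria for discontinuation are voluntary withdrawal of consent, pregnancy, or non-compliance with the study protocol as judged by the investigator".
- **Statistics**: "the analysis will be based on data from patients who complete the first treatment period and at least 6 months of the second treatment period". The reason given is that long participation guards against catching a patient in an unusually good or bad phase. The section then describes a negative binomial or Poisson model and adds: "Individual differences in the observation period will be adjusted for in the analysis".

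Two features of the Design section matter here. The study is a "prospective, randomised, open, blinded endpoint (PROBE), multicentre, cross-over trial", so treatment is known to patient and investigator. On timing, "Endpoints are assessed during the last 9 months of each treatment arm, the first 3 months being used for run-in".

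**The concern.** The Statistics rule is the only event-count analysis described, and it carries no label that would make it secondary to an intention-to-treat analysis. An analyst following Subjects keeps a patient who leaves at month 10. An analyst following Statistics drops that patient. The article thus leaves a choice between two primary results.

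The narrower set is also conditioned on something that happens after randomisation. Treatment is open, and one route out is "non-compliance with the study protocol as judged by the investigator", a decision taken by someone who knows the regimen. Blinded telephone interviewers protect the classification of episodes; they do not protect the decision about who remains in the analysis. If staying in the trial depends on how a patient responds to one regimen, the rate ratio in near-completers need not equal the ratio in those randomised.

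**Working it through.** **1. The plan's own figures.** The Power calculation section states: "Setting power to 80% and a test level of 5%, the total number of events needs to be 1220". Under the alternative, P = 1/(1 + 0.85) = 0.5405. A two-sided 5% exact binomial test has 80.5% power at 1220 events, so the figure reproduces. Patients: 1220/(2.09 × 1.85) = 315.5, against 315 stated. Dropout: 315/0.85 = 370.6, against 370 stated. There is no arithmetic error in this chain, and the inflation from 315 to 370 replaces lost numbers. It says nothing about who is analysed.

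**2. The two rules side by side.** Each period lasts 12 months, and endpoint time starts after month 3 of a period, that is, after study months 3 and 15. The Statistics rule requires 12 + 6 = 18 months, if the 6 months count from the start of period 2.

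| Patient leaves | Endpoint time held | Subjects | Statistics |
|---|---|---|---|
| months 0–3 | none | no data to include | excluded |
| months 3–15 | period 1 only | included | excluded |
| months 15–18 | both periods | included | excluded |
| after month 18 | both periods | included | included |

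The rules agree in the last row and, in practice, the first. They conflict in the two middle rows. A patient leaving at month 17 has 9 + 2 = 11 endpoint months and is dropped; one leaving at month 18 has 9 + 3 = 12 and is kept.

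**3. How many patients.** Planned dropout is 0.15 × 370 = 55.5. Assumption: constant hazard, so the proportion still in the trial at month t is 0.85^(t/24).

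- Month 3: 0.85^(3/24) = 0.9799
- Month 15: 0.85^(15/24) = 0.9034
- Month 18: 0.85^(18/24) = 0.8852

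Expected leavers:

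- months 0–3: 370 × (1 − 0.9799) = 7.4
- months 3–15: 370 × (0.9799 − 0.9034) = 28.3
- months 15–18: 370 × (0.9034 − 0.8852) = 6.7
- before month 18 in total: 42.5
- after month 18 (stay in under both rules): 55.5 − 42.5 = 13.0

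The conflict therefore concerns about 28 + 7 = 35 patients with usable endpoint time, and some 7 more have none.

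**4. Size of bias: illustration only.** The document gives no rate or treatment effect for leavers. Let near-completers have ratio 0.85, let all 15% be excluded (an upper limit), and let leavers have true ratio R and m times the baseline rate. The ratio in all randomised is (0.85 × 0.85 + 0.15m × R)/(0.85 + 0.15m).

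| R | m = 1 | m = 2 |
|---|---|---|
| 0.70 | 0.83 | 0.81 |
| 0.85 | 0.85 | 0.85 |
| 1.00 | 0.87 | 0.89 |
| 1.30 | 0.92 | 0.97 |

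The ratio can move either way, and it does not move when R = 0.85. The formula also credits leavers with full follow-up that would not exist, so it is not the gap that two analysts would report.

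**5. What the remedy achieves, under assumptions.** Simulated trials of 370 patients used gamma frailty with variance 1 and a monthly dropout hazard of 0.0075 times the patient's current relative event rate. With no spread between patients in treatment effect, near-completers gave 0.85 against a true 0.85. With an assumed SD of 0.5 in the patient log-ratio, near-completers gave about 0.82 to 0.83, and the all-randomised model about 0.83, against 0.85. In one run the figures were 0.826, 0.831 and 0.851, so the remedy recovered 0.005 of a gap of 0.025, about one fifth. The standard error of the log ratio was near 0.07.

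**The case against.** Requiring data from both periods is common in a cross-over trial. The design rests on comparing each patient with himself or herself, and the power calculation conditions on each patient's total events; in that comparison a single-period patient adds little or nothing. The adjustment for observation time also has work to do inside the restricted set, because period 2 follow-up there runs from 6 to 12 months. So that sentence does not by itself make the restriction pointless. This stands, and it could justify a labelled completer set. It does not make the set intention-to-treat, and it does not explain dropping patients who already have endpoint time in both periods.

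Statistics speaks of the analysis without calling it primary, and a fuller document may define analysis sets. But the conflict is between two rules that the article states, and a later plan would have to override one of them.

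Three stronger readings are tempting, and the document does not support them.

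- *A 15% reduction would really be a much smaller one.* That needs leavers to respond worse than completers, which nothing in the article shows.
- *All 55 dropouts would be lost from the analysis.* Those leaving after month 18 stay in.
- *Severe hypoglycaemia drives patients out.* This is plausible, but it is not among the listed discontinuation criteria.

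**Conclusion.** The concern holds as a conflict over the analysis population. For patients who leave before about month 18, Subjects and Statistics cannot both be followed, and the set in Statistics is chosen on post-randomisation events in an open trial. Month 18 assumes that the 6 months run from the start of period 2. The article's 15% dropout, with a constant hazard assumed, puts about 42 of 370 patients outside the Statistics set, about 35 of them with endpoint time.

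The result is exposed to selection, but the article does not show it to be biased. Direction and size are unknown, and with a common treatment effect in leavers and completers there is essentially no bias. The case for settling the point rests on having one pre-stated primary population, not on a predicted shift in the estimate.

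**What to change.** In Statistics, replace the restriction with one primary set: all randomised patients with any endpoint time (after month 3 of a period), analysed by assigned treatment, with log observation time as offset and a patient-level effect so that single-period patients contribute. Keep the current set, period 1 completed plus at least 6 months of period 2, as a labelled sensitivity analysis, and say from which point the 6 months count. Subjects can then stand as written.

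A supportive analysis of months 0–12 of each period would bring in those who leave during run-in. It is optional, because the plan leaves run-in out on purpose.

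The cost is a change of wording and one further model run on data already collected. There are four drawbacks:

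- Single-period patients add little to the within-patient contrast.
- The model reduces but does not remove bias from outcome-dependent dropout.
- The estimate may be slightly less favourable.
- The Timeline section puts the last visit in the past, so the choice of set needs a dated justification, and both results should be reported.

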## Background

Severe hypoglycaemia still represents a significant risk for many patients with type 1 diabetes. The condition is feared by patients [1,2] and relatives [3] and remains a major barrier in achieving recommended glycaemic targets [4]. Moreover, severe hypoglycaemia may, although rarely, lead to permanent brain damage or death [5]. The frequency of severe hypoglycaemia in type 1 diabetic populations is 1–1.7 episodes per patient-year [6-14]. The distribution of episodes is, however, very skewed. Thus, 20% of patients with type 1 diabetes experience two or more episodes of severe hypoglycaemia per year [15]. Once prone to recurrent severe hypoglycaemia, patients often remain so throughout their life.

Insulin analogues were developed to improve treatment of insulin-treated diabetes with respect to glycaemic control and avoidance of hypoglycaemic episodes. Short-acting insulin analogues (aspart, lispro and glulisine) were designed to mimic the fast physiological postprandial insulin release and long-acting insulin analogues (detemir and glargine) were designed to mimic the basal continuous insulin release with minimal peak action, thereby leading to a presumed decreased risk of hypoglycaemia. The effect of insulin analogues on glycaemic control has been documented in large trials [16,17]. However, for several reasons the impact of insulin analogues on the frequency of severe hypoglycaemia is less clear. Firstly, most studies comparing the effects of human insulin with those of insulin analogues specifically exclude patients at risk of severe hypoglycaemia, such as patients with previous severe events or impaired hypoglycaemia awareness, from participation [18-21]. This renders the trials insufficiently statistically powered to detect differences in the frequency of severe hypoglycaemia and the conclusions from these studies can not readily be extrapolated to patient groups prone to severe hypoglycaemia. Secondly, hypoglycaemia is often less well defined and detected, at best as a secondary endpoint, with reports including a mixture of mild, severe, and asymptomatic hypoglycaemia. Thirdly, severe hypoglycaemia should be analysed according to a statistic model that takes into account the much skewed distribution of episodes e.g. negative binomial or zero-inflated models [22].

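### The primary model as stated leaves negative binomial or Poisson open and does not link a patient's two periods; under the negative binomial option the precision of the crossover is lost

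*Protocol article*

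**What the plan says.** The Statistics section of the protocol article states the primary model in some detail. On the family: "An analysis in a negative binomial distribution or Poisson model will be used to describe the number of events through a log link function". On the predictors: "as a linear function of treatment, treatment period, HbA_1c_ levels and other relevant variables", the others being "state of hypoglycaemia awareness, C-peptide status, age, duration of diabetes, daily insulin dose". On follow-up time: "Individual differences in the observation period will be adjusted for in the analysis". It names no patient effect, conditioning, clustering or robust variance, and no rule for choosing between the two families.

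Three other statements bear on this:
- The same section justifies the design because it can "compare the two treatment modalities within the same person, thereby minimising between-patient variation".
- The Power calculation assumes Poisson counts in each period and reduces them to a binomial: "Based on the total number of observed events for each individual patient".
- The Background asks for a model that "takes into account the much skewed distribution of episodes e.g. negative binomial or zero-inflated models".

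**The concern.** The trial is designed and sized as a paired comparison, but the model as written has nothing that pairs the counts. Adjusting for observation time does not do so, and the listed patient characteristics do so only as far as they explain why some patients have more events than others.

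The two permitted families handle the missing link differently. The negative binomial absorbs between-patient spread into its dispersion parameter and then treats the two periods as independent, so that spread enlarges the standard error of the treatment effect. The Poisson model ignores the spread, which is harmless in one situation and not in another. On the same data the two can give standard errors that differ by a factor of about 1.4 to 2.2 (between-patient variance 0.5 to 2). With no selection rule, the primary conclusion could depend on which one is reported.

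**Working it through.** **Inputs from the Power calculation.** Human insulin mean μ1 = 2.09 per 9 months; rate ratio 0.85, so μ2 = 2.09 × 0.85 = 1.7765; 1220 events; n = 315 patients; 80% power; 5% level (taken as two-sided, which reproduces the figure).

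**Assumed inputs, not in the article.** Each patient's rate carries a gamma factor with mean 1 and variance k (range 0.2 to 2). A separate gamma factor for each period has variance kw (range 0 to 0.5).

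**1. The stated sample size reproduces, as a paired analysis.** The exact two-sided binomial test of 1/2 against 1/1.85 = 0.5405 with 1220 events has power 80.5% at an actual level of 4.8%. Patients: 1220 / (2.09 × 1.85) = 315.5, against 315 stated. With dropout: 315 / 0.85 = 370.6, against 370 stated.

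**2. Paired precision (kw = 0).** The variance of the log rate ratio is (1/μ1 + 1/μ2)/n = (0.4785 + 0.5629)/315 = 0.003306, so SD = 0.0575. The effect is −ln 0.85 = 0.1625. Power = Φ(0.1625/0.0575 − 1.96) = 81%.

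**3. Negative binomial without a patient term (kw = 0).** The model-based variance is (1/μ1 + 1/μ2 + 2k)/n. The estimate still varies with SD 0.0575, because the patient factor cancels in the comparison. Power = Φ(0.1625/0.0575 − 1.96 × SE/0.0575).

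| k (assumed) | SE | SE / true SD | Power |
|---|---|---|---|
| 0.2 | 0.068 | 1.18 | 70% |
| 0.5 | 0.080 | 1.40 | 53% |
| 1 | 0.098 | 1.71 | 30% |
| 2 | 0.127 | 2.20 | 7% |

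Simulation (600 trials per setting, 315 completers) gave 53%, 31% and 5% at k = 0.5, 1 and 2. Type I error there was 0.3% or less. With kw = 0.25 to 0.5 at k = 1 it was 1.2% to 2.5%, still below 5%.

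**4. Poisson without a patient term, kw = 0.** Between-patient spread adds 2k to the sum of the two variances, and the covariance between a patient's periods removes 2k. The model SE is therefore right. Simulation: SE 0.058, power 80–82%, type I error scattered around 5%.

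**5. Poisson without a patient term, kw > 0.** The true variance becomes [1/μ1 + 1/μ2 + 2kw(1 + k)]/n, while the model still reports (1/μ1 + 1/μ2)/n. Under the null both means are 2.09 and 1/μ1 + 1/μ2 = 0.957. Type I error = 2[1 − Φ(1.96 × √(0.957/(0.957 + 2kw(1 + k))))].

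| kw (assumed) | k = 0.5 | k = 1 |
|---|---|---|
| 0.1 | 9% | 10% |
| 0.25 | 14% | 17% |
| 0.5 | 22% | 26% |

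Simulation at k = 1 gave 17% and 28% for kw = 0.25 and 0.5. Conditioning on patient totals (a patient fixed effect) left these at 17% and 28%.

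**6. Poisson with patient-clustered robust variance.** Type I error was 4.3% to 7.5% over six settings of 600 trials (Monte Carlo error about 1–2 points), and 4.4% to 5.8% in a larger run. With kw = 0 it kept the paired power. With kw = 0.25 the step 5 variance gives Φ(0.1625/√((1.041 + 0.75)/315) − 1.96) = 58% at k = 0.5, and with 1.00 in place of 0.75, 52% at k = 1 (56% in the 600-trial simulation).

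**The case against.** The strongest reply is that this is a condensed article. A list of explanatory variables describes the mean, and random effects, clustering and the variance estimator are details that a full plan commonly supplies. The same section speaks of comparison within the person, and nowhere does the article say that the periods are treated as independent. This stands as a limit: a reader might infer that the trial did discard the pairing, and the article does not show that. What remains is printed text, namely an unresolved choice of family and a stated predictor list that falls short of the stated rationale.

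A reader might also infer that the Poisson option gives intervals that are too narrow. The documents do not support that as a flat statement. The Power calculation assumes Poisson counts in each period, the Statistics section assumes that the patient's status is the same in both, and under those assumptions the plain Poisson standard error is correct. Inflation needs variation between a patient's periods, for which no figure is given. Nor is the missing patient term its cause, since a patient fixed effect does not cure it.

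A third tempting step is to derive k from the Background (20% of patients with two or more episodes, mean 1–1.7 per year). A gamma-Poisson fit gives k of about 0.69 to 1.23 among such patients and negative binomial power of 22–44%. The same fit, however, gives those patients 3.6 to 7.7 events per year, not the 2.8 used for sample size, so that range mixes two populations. The listed covariates would also lower k somewhat.

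Finally, the negative binomial error is conservative and creates no false positives, and choosing between the families by observed overdispersion is common practice. Both are true. Neither restores the lost power or supplies the missing rule.

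**Conclusion.** The point holds for the model as stated. The family is open, no rule selects it, and the predictors do not link a patient's two counts, in contrast to the within-person rationale and the paired power calculation. Followed literally, the negative binomial option has a standard error about 1.2 to 2.2 times too large and power of about 70% down to 7%, against 81% paired, for assumed k from 0.2 to 2.

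The Poisson option is sound under the protocol's own assumptions. It becomes anti-conservative only if rates vary between periods: type I error roughly 8–10%, 14–17% and 22–28% at assumed variances of 0.1, 0.25 and 0.5, with k between 0.5 and 1.

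Both k and kw are assumptions, as is the gamma form, and the calculations leave out covariates and unequal follow-up. It is not shown that the open choice would be used to favour a result, only that the two permitted models can disagree enough to matter for the primary endpoint.

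**What to change.** Before analysis, name one primary model in the Statistics section and remove the open alternative. Use a Poisson log-linear model with treatment, period, the stated covariates and a log(observation time) offset, fitted by GEE with robust variance clustered on the patient. Make a negative binomial mixed model with a random patient intercept the sensitivity analysis. If the full plan already contains a patient term, the article needs only a sentence saying so and naming the family.

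This changes wording and needs no new data. The real cost is candour about power: if rates vary between periods, the interval is wider and power falls below the stated 80%, to about 52–58% at an assumed variance of 0.25 (k between 0.5 and 1). A plain Poisson model would hide that uncertainty.

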## Objective

The primary objective is to evaluate the effect of treatment with insulin analogue and human insulin over the preceding 9 months in each treatment arm on the incidence of severe hypoglycaemia in patients with type 1 diabetes prone to hypoglycaemia.

The secondary objectives are – with reference to the ADA criteria for classification of hypoglycaemia [26] – to evaluate the effects of insulin analogue and human insulin from 3 to 12 months of treatment on the incidence of:

· documented (mild) symptomatic hypoglycaemia.

· asymptomatic hypoglycaemia.

· severe hypoglycaemia, documented symptomatic hypoglycaemia, and asymptomatic hypoglycaemia during daytime.

· severe hypoglycaemia, documented symptomatic hypoglycaemia, and asymptomatic hypoglycaemia during night-time

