#### HbA1c and plasma glucose

At every visit to the outpatient clinic (totalling 9 visits per patient) blood samples are drawn to measure HbA1c levels (analysed centrally at Steno Diabetes Center) and random plasma glucose concentrations (measured locally).

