### Laboratory analysis

At the first visit fasting C-peptide, haemoglobin, haematocrit, plasma creatinine, plasma sodium, and plasma potassium, thrombocyte count, white blood cell count, alanine aminotransferase, alkaline phosphatase, bilirubin, total cholesterol, high and low density lipoprotein cholesterols, triglycerides, thyroid-stimulating hormone TSH, T4 and T3 are measured. These analyses are repeated after 1 year (before changing insulin regimen) and after 2 years (final visit). Participants with C-peptide concentrations below 300 pmol/l or stimulated (venous blood glucose concentration >12 mmol/l) C-peptide concentrations below 600 pmol/l were considered C-peptide negative. At every visit HbA1c and random plasma glucose are measured. Biobank samples (serum, plasma and DNA) are gathered at baseline and six times (three times in each insulin regimen) during the study. Urinary sodium and albumin concentration are determined in urine samples collected from two separate nights at baseline and repeated after 1 year (before shifting insulin regimen) and after 2 years (final visit). HbA1c is measured centrally at Steno Diabetes Center using High Performance Liquid Chromatography method on a Tosoh Automated Glycohemoglobin Analyzer. C-peptide is measured with an AutoDELFIA C-peptide kit (detection limit 5 pmol/l). An ACTH stimulation test was undertaken at the first visit. All other analyses are performed locally by routine methods.

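### The only event-count model adjusts for HbA1c and daily insulin dose without fixing them at baseline; if on-treatment values are used, it does not target the total effect named in the objective

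*Protocol article*

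**What the plan says.** The Objective section sets the primary aim as "to evaluate the effect of treatment with insulin analogue and human insulin over the preceding 9 months in each treatment arm"; the outcome is how often severe hypoglycaemia occurs. No aim is stated to estimate an effect at equal HbA1c or equal dose.

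The Statistics section describes a negative binomial or Poisson model with a log link. Its terms are treatment, period and, for HbA1c and the remaining covariates, "levels and other relevant variables (state of hypoglycaemia awareness, C-peptide status, age, duration of diabetes, daily insulin dose". No measurement time is given for any of them, and no model without them is stated.

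Three other statements bear on timing:
- HbA1c and plasma glucose section: "At every visit to the outpatient clinic (totalling 9 visits per patient) blood samples are drawn to measure HbA1c levels". Laboratory analysis repeats this: "At every visit HbA1c and random plasma glucose are measured".
- Design, on dose: "Doses of insulin are adjusted according to individual patient need at the discretion of the investigator".
- Design, on glycaemic control: "a treat-to-target design is deliberately not used in order not to intervene with present glycaemic control and everyday clinical practice".

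**The concern.** HbA1c and daily dose can both be changed by the insulin a patient is assigned, and both plausibly bear on the risk of severe hypoglycaemia. Values taken during a treatment period may therefore lie on the path from treatment to outcome. Holding them constant removes whatever part of the effect runs through them.

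What remains would be an effect at equal HbA1c and equal dose, and randomisation does not protect that quantity either. Investigators who know the treatment adjust dose to patient need, so dose and HbA1c may be partly consequences of earlier hypoglycaemia. Conditioning on them then brings in confounding.

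The headline answer is at stake. A real reduction could be partly adjusted away, or a benefit that exists only at equal HbA1c could be reported as the benefit of the insulin.

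**Working it through.** **Timing.** Visits are three-monthly over two years, so 24/3 + 1 = 9 visits, matching the stated number. Randomisation is at the end of the first, so 8 of the 9 HbA1c values are post-randomisation. The model places HbA1c beside treatment period, and a model with one count per period naturally takes one HbA1c per period. A value fixed per patient would add little to a within-patient contrast. This is an inference; the article does not state it.

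**Does the design keep HbA1c equal between treatments?** No mechanism does so: "a treat-to-target design is deliberately not used". The Background says large trials have documented an effect of analogues on glycaemic control.

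**The plan's own figures.** The Power calculation uses the split of events between treatments, with neither HbA1c nor dose in it.
- p = 1/(1 + 0.85) = 0.5405 against 0.5. A two-sided exact binomial test on 1220 events has 80.5% power (actual level 0.048).
- 1220/3.84 = 317.7; with unrounded 2.09 x 1.85 = 3.8665, 1220/3.8665 = 315.5, against the stated 315.
- 315/0.85 = 370.6, against the stated 370.

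These reproduce within rounding. The issue is what the model estimates, not the sample size arithmetic.

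**Size of the HbA1c shift.** Let b be the change in log event rate per 1 %-point HbA1c, and d the HbA1c difference, analogue minus human insulin. The documents give neither, so both are assumptions. On the log scale, total effect = direct effect + b x d, so the adjusted rate ratio is 0.85/exp(b x d).

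| b | d = -0.3 | d = -0.2 | d = -0.1 | d = +0.1 | d = +0.2 | d = +0.3 |
|---|---|---|---|---|---|---|
| -0.1 | 0.825 | 0.833 | 0.842 | 0.859 | 0.867 | 0.876 |
| -0.2 | 0.800 | 0.817 | 0.833 | 0.867 | 0.885 | 0.903 |
| -0.3 | 0.777 | 0.800 | 0.825 | 0.876 | 0.903 | 0.930 |

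The extremes are 0.85/exp(0.09) = 0.85/1.094 = 0.777 and 0.85/exp(-0.09) = 0.85/0.914 = 0.930. At d = 0 there is no shift. Because d takes both signs, reversing the sign of b leaves the range unchanged.

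Holding events at 1220, approximate power is Φ(√1220 x |ln RR|/2 - 1.96). It runs from 99% at 0.777 to 24% at 0.930. The 99% is no gain, since it refers to a different quantity.

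**Simulation of the mechanism** (Poisson crossover, gamma frailty, 40,000 patients, true total rate ratio 0.85, estimates accurate to about 0.01):

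| b, d | Unadjusted | Baseline HbA1c | On-treatment HbA1c | Direct effect |
|---|---|---|---|---|
| -0.2, -0.2 | 0.853 | 0.840 | 0.808 | 0.817 |
| -0.2, +0.2 | 0.843 | 0.853 | 0.884 | 0.885 |
| -0.3, -0.3 | 0.853 | 0.856 | 0.776 | 0.777 |

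Baseline adjustment keeps the total effect; on-treatment adjustment moves to the direct effect. The simulation contains no feedback from hypoglycaemia to HbA1c or dose, so it leaves the confounding out. No figure is offered for daily dose, because the documents give nothing from which to size it.

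**The case against.** The strongest objection is that the article never says the values are on-treatment. Age and diabetes duration in the same list are in effect baseline variables, awareness is described only at visit 1, and C-peptide is first measured there. No section describes recording dose during the study. A journal article may leave the choice of visit to a fuller document. All of this stands as to timing: a reader might infer that the plan definitely conditions on post-randomisation variables, including awareness, and the text does not support that. It does not dispose of the point, because the article itself names the covariates, attaches no baseline limit, and offers no other model.

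A second objection is that the section does not label this fit as the sole confirmatory estimate, and that the sizing is unadjusted. That is fair, but no unadjusted analysis is stated either.

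Third, the size is assumed. The Design section says the best obtainable control is sought in both periods, which is compatible with a small HbA1c difference. That also stands. A reader might infer a known bias, in a known direction, large against the 15% minimal relevant difference. The documents support neither a direction nor a size.

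**Conclusion.** The concern holds conditionally. As written, the plan permits, and most naturally describes, a model that conditions on period-specific HbA1c and dose. On that reading its treatment coefficient does not target the total effect on severe hypoglycaemia and may be confounded as well. For HbA1c alone, a true rate ratio of 0.85 would become about 0.78 to 0.93, entirely under the assumed slope and difference. The shift is nil if treatment leaves HbA1c unchanged; the contribution of dose is unquantified. If the sponsor means baseline values, this bias is absent and the text need only say so.

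**What to change.** State the primary model as treatment, period, patient effect and log observation time. Restrict any covariates to values from visit 1. A value from the 12-month visit should not serve as baseline for the second period, because it was measured under the first insulin. If daily dose was not recorded at visit 1, leave it out of the primary model.

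Move on-treatment HbA1c and daily dose, and any awareness score collected during the study, to a model labelled secondary or exploratory. Beside the primary result, report the between-treatment differences in HbA1c and daily dose with confidence intervals, so that readers can judge how far glycaemic control moved with the event rate.

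The cost is analysis wording only; no visit, measurement or sample size changes, and the adjusted model can still be shown. The article gives November 2011 for the last visit, so the choice should be recorded before anyone sees results by treatment.
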